## Abstract

**Background:**

Aging has been associated with a progressive loss of skeletal muscle quality, quantity and strength, which may result in a condition known as sarcopenia, leading to a decline in physical performance, loss of independence and reduced quality of life. While the cause of impaired physical functioning observed in elderly populations appears to be multifactorial, recent evidence suggests that age-associated alterations in gut microbiota could be a contributing factor. The primary objective will be to assess the effects of a dietary synbiotic formulation on sarcopenia-related functional outcomes such as handgrip strength, gait speed and physical performance within older individuals living independently. The secondary objective will be to examine associations between changes in gut microbiota composition, functional performance and lean muscle mass.

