#### Secondary aims

We hypothesize 16 weeks of ingesting a synbiotic preparation compared to placebo will result in statistically significant improvements (within-group and between-group) in:(6)Muscle mass and body composition (LBM, ALM, total and regional body FM and FFM)(7)Muscle quality (CSA, MT, EI, FL, and PA of *Rectus femoris* and *Vastus intermedius* muscles)(8)Fecal microbiota composition and diversity(9)Untargeted fecal and serum metabolomics

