### Statistical analyses and power

This estimated sample size for the main outcome measures of physical performance was based on an assumed correlation of 0.7 between the pre- and post-intervention outcome measures, and an effect size of Cohen’s *d* = 1.2 for gait speed based on data from Román et al. [29] that examined the effects of a multi-strain probiotic on gait speed and the TUG test in a study cohort of 35 (17 and 18 in treatment and placebo groups, respectively). To have a power of 80% and a significance level of 5%, our study aims to enrol an estimated sample size of 74 participants (37 per group), taking into account a conservative ~ 30% dropout rate.

The study hypotheses will be addressed using a hierarchical linear model analysis to test for significant differences between the two comparative groups (intervention and placebo) over time. A primary intention to treat (ITT) analysis will be conducted on all the participants who complete the trial. Additionally, a secondary analysis will be carried out to include only participants who consumed ≥ 90% of their supplement over the course of the intervention period. Between-group comparisons will be made using linear models and statistical significance set at *p* < 0.05. Where there are significant group xtime interactions, planned contrasts will compare changes from baseline under each intervention. Similar tests will be performed for the secondary hypotheses, using appropriate transformations if these measures exhibit non-normal distributions across time points. This analysis will allow for the control of any baseline group differences and to test for moderation effects in terms of these variables over time. Analysis of microbial community composition will be conducted using Phyloseq and vegan package in R version 3.6.1 as per protocol.

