Wilcoxon’s signed-rank test, Spearman’s rank correlation (p), Pearson’s correlation (r), multiple linear regression, and/or linear mixed models will be used to examine associations and appropriate comparisons depending on the distributions of the variables. Relationships between markers of functional performance, ordinations of stool microbiota composition, and stool/plasma metabolites will also be assessed using the Structural Equation Model to enable causal assumptions to be interpreted between variables to ensure these relationships are not “coincidental” and linear mixed models. All mixed models will include the subject as a random factor and time as a continuous covariate. Backward stepwise regression will be used to identify the strongest predictors of changes in aspects of functional performance. The false discovery rate for all tests will be controlled by adjusting *P* values using the Benjamini–Hochberg procedure. Adjusted *P* values will be presented as *Q* values. Statistical analyses will be completed using SPSS v.26. 11.2.2

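### Structural equation modelling cannot guarantee that gut-muscle relationships are real at any sample size, and backward stepwise selection overstates the predictors it keeps

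*Protocol article*

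**What the plan says.** In the protocol article, section Statistical analyses and power, two statements matter here.

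- On SEM: "Relationships between markers of functional performance, ordinations of stool microbiota composition, and stool/plasma metabolites will also be assessed using the Structural Equation Model". The purpose given is "to enable causal assumptions to be interpreted between variables to ensure these relationships are not" coincidental.
- On predictors: "Backward stepwise regression will be used to identify the strongest predictors of changes in aspects of functional performance".

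The same paragraph adds a multiplicity safeguard: "The false discovery rate for all tests will be controlled by adjusting" P values with the Benjamini-Hochberg (BH) procedure.

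The objective these analyses serve is worded more modestly. The Abstract (Background) says: "The secondary objective will be to examine associations between changes in gut microbiota composition, functional performance and lean muscle mass". Possible predictors include high-dimensional data, since the Secondary aims list "Untargeted fecal and serum metabolomics".

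On size, "our study aims to enrol an estimated sample size of 74 participants (37 per group"), "taking into account a conservative ~ 30% dropout rate".

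**The concern.** The SEM sentence credits the method with something it cannot do. The analyst supplies the arrows, and the model estimates their strength on the premise that they are right. Randomisation protects the effect of arm on microbiota and of arm on function. It does not protect the path from microbiota or metabolites to function. Diet, activity and general health can drive both ends of that path, and function can influence the gut rather than the reverse.

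The stepwise sentence names a method poorly suited to its stated task. Backward elimination chooses variables and tests them on the same data, so the p-values and R-squared of the final model look better than they are. Adjusting those p-values afterwards does not undo the selection.

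At stake is the interpretation of a stated secondary objective. If the section is followed as written, confounded paths may be read as causal, and chance predictors may be listed as the strongest.

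**Working it through.** **Inputs from the article.** 74 participants, about 30% dropout, 1:1 allocation. Completers: 74 × 0.70 = 51.8, about 52. The figure of 74 was sized for a group effect on gait speed, not for these analyses. It also does not follow from the stated inputs: for d = 1.2, two-sided 5% and 80% power, 2 × (1.96 + 0.84)² / 1.2² gives 11 per arm, and 11 / 0.70 gives 16, not 37. That is a separate matter. Only 74 and 30% are used below.

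**Inputs assumed.** The article gives no number of candidates, removal threshold or SEM structure. The values below are illustrative ranges.

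**Step 1: can a fitted path show that a relationship is not coincidental?** Let T be arm, U an unmeasured cause, and e₁ and e₂ independent standard normal errors.

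- Microbiota: M = 0.5T + 0.6U + 0.8e₁
- Function: Y = 0.6U + 0.8e₂, so M has no effect on Y

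Regressing Y on M and T estimates cov(M,Y | T) / var(M | T) = 0.36 / (0.36 + 0.64) = 0.36, although the truth is 0.

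| N | Path significant at 5% | Mean estimate |
|---|---|---|
| 52 | 76% | 0.36 |
| 74 | 89% | 0.36 |
| 1000 | 100% | 0.36 |

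The bias does not shrink with N; a larger sample only makes the wrong answer more certain. Small N adds imprecision. An observed correlation of 0.30 has a 95% interval of 0.03 to 0.53 at N = 52 and 0.08 to 0.49 at N = 74.

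**Step 2: backward elimination on pure noise.** N = 52, removal at p > 0.10. Entries are the share of runs with at least one false predictor.

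| Candidates | Before BH | BH over survivors only | BH on final-model p-values, counting all candidates |
|---|---|---|---|
| 10 | 68% | 38% | 8% |
| 20 | 91% | 63% | 16% |
| 30 | 97% | 80% | 41% |

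Repeat runs differ by a few points (37% to 41% in the last cell). Three observations follow.

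- The first column is close to plain multiplicity: 1 − 0.9^k gives 65%, 88% and 96% for k = 10, 20 and 30. It hardly changes at N = 74 (67%, 90%, 97%).
- Inflation of fit does depend on N. Mean apparent R-squared from noise is 0.09, 0.21 and 0.35 at N = 52, against 0.07, 0.14 and 0.23 at N = 74.
- If removal were at p > 0.05, BH at 5% over survivors would change nothing, because every survivor already has p ≤ 0.05.

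With 5 candidates and removal at p > 0.05, a false predictor is kept in 23% of runs before BH.

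**Step 3: backward elimination when real predictors exist.** 20 candidates with pairwise correlation 0.5, three of them real (coefficients 0.4, 0.3, 0.2), removal at p > 0.10. The exact true set is found in 0.4% of runs at N = 52 and 1.8% at N = 74. The strongest real predictor is dropped in 32% and 21%.

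**The case against.** **Detail left to the analysis plan.** The candidate list, threshold and validation may sit in the full protocol or an analysis plan that is not shown. This stands: their absence is no finding, and a short pre-specified list would remove much of the stepwise problem. It does not rescue the SEM sentence, which is an affirmative claim that no further document could make true.

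**The planned safeguard.** A reader might take 68/91/97% as the error rate under the plan. It is not, because BH is planned for all tests. With BH the rate depends on how it is applied, and it falls to about 4% to 5% if BH is used on the full-model p-values before any selection. That last route, however, no longer rests on the stepwise result.

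**Sample size.** A reader might infer that 52 to 74 participants are too few and that a larger trial would cure both faults. Step 1 shows otherwise for SEM, and the before-BH column of Step 2 barely depends on N.

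**Timing of measurement.** A reader might infer that gut and function data exist only after randomisation. Study assessments and the stool section schedule function, blood and stool at baseline and at weeks 8, 16 and 20. Diet is recorded for all four visits, and the Fig. 1 legend lists a physical activity scale. Named confounders can therefore be adjusted for; unmeasured and time-varying ones cannot.

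**Consequence.** A reader might infer that the trial will present a mechanism as established. The documents do not go that far. The Abstract speaks of associations, the Discussion is hedged, and none of the numbered hypotheses is about mediation.

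**Conclusion.** The point holds in two parts of unequal strength.

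The SEM claim is wrong as written, at any sample size. That conclusion follows from the design, in which only the arm is randomised, and from what the method assumes. The 76% to 100% figures illustrate it under an assumed unmeasured cause with loading 0.6 on each variable.

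The stepwise part is a caution whose size is conditional. For 10 to 30 noise candidates and removal at p > 0.10, false predictors survive in 8% to 41% of runs under the stricter of the two BH applications to the final model, and in 38% to 80% under the looser one. It is milder with few candidates, and the real number is not stated.

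Both parts concern secondary, associational analyses. The randomised primary comparison is untouched.

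**What to change.** 1. Delete the statement that SEM guarantees relationships are not coincidental. Say instead that its causal structure is assumed.
2. Label the SEM and predictor analyses exploratory and associational, in line with the Abstract.
3. Adjust any SEM for arm, baseline values, and the diet and activity data already collected. Report how sensitive the paths are to unmeasured confounding.
4. Replace backward stepwise regression with a short predictor list fixed in advance, or with penalised regression and resampling that reports cross-validated error and selection frequencies.

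The cost is modest analysis work and a more cautious mechanistic conclusion. No new data collection is needed.

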**Methods:**

Seventy-four elderly (60–85 years) participants will be randomized in a double-blind, placebo-controlled fashion to either an intervention or control group. The intervention group (*n* = 37) will receive oral synbiotic formulation daily for 16 weeks. The control group (*n* = 37) will receive placebo. Assessments of physical performance (including Short Physical Performance Battery, handgrip strength and timed up-and-go tests) and muscle ultrasonography will be performed at 4 time points (baseline and weeks 8, 16 and 20). Likewise, body composition via bioelectric impedance analysis and blood and stool samples will be collected at each time point. Dual-energy X-ray absorptiometry will be performed at baseline and week 16. The primary outcomes will be between-group changes in physical performance from baseline to 16 weeks. Secondary outcomes include changes in body composition, muscle mass and architecture, fecal microbiota composition and diversity, and fecal and plasma metabolomics.

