#### Study duration

Participant involvement will be approximately 22 weeks. This will consist of a screening period of no longer than 2 weeks, a 16-week intervention period, and a 4-week follow-up period. Each participant will attend a screening visit, during which eligibility will be confirmed and informed consent will be obtained. Study investigational product (IP) will be initiated within 2 weeks following successful screening (at baseline visit). Each participant will subsequently attend 3 further visits: mid-intervention at 8 weeks, an end-of-intervention visit at 16 weeks, and a follow-up visit at 20 weeks. Study endpoints will be evaluated at each visit as discussed below. The trial design is outlined in Fig. 2.

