### Study assessments

Data collection will include Short Physical Performance Battery (SPPB), handgrip strength (HGS), timed up and go (TUG) test, as well as body composition and muscle morphology. These outcomes will be assessed at 4 time points (baseline and weeks 8, 16, and 20). Venous blood will be collected at 4 time points by venipuncture of the median cubital vein after overnight fasting using commercial collection tubes. Two 4.5-mL samples will be taken in EDTA and two 8.5mL SST collection tubes. Samples will be rested for 30 min at room temperature followed by centrifugation at 3000 × *g* for 15 min at 4°C after which serum and plasma will be collected into 0.5mL aliquots and stored at − 80°C until analysis. Participants will be carefully instructed on the procedures for fecal sample collection. Participants will be given stool collection kits at each visit, to be collected at home and returned at the following visit, as described below.

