### Hypotheses and study endpoints

#### Primary aims

We hypothesize 16 weeks of ingesting a synbiotic preparation compared to placebo will result in statistically significant improvements (within-group and between-group) in:4-m gait speedStanding balanceRepeated chair risesTimed up and go Handgrip strength

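### Read literally, the continuous-time rule turns the primary test into a straight-line slope that, if off-treatment week 20 is in the model, does not estimate the week-16 between-group change defined as primary

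*Protocol article*

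**What the plan says.** The Methods part of the abstract defines the target: "The primary outcomes will be between-group changes in physical performance from baseline to 16 weeks". The primary aims under Hypotheses and study endpoints take the same view, since they concern the effect of 16 weeks of ingestion.

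Study duration gives "a 16-week intervention period, and a 4-week follow-up period", so the week-20 visit falls after dosing has ended. Study assessments has the Short Physical Performance Battery, handgrip strength and timed up-and-go measured at baseline and weeks 8, 16 and 20.

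Statistical analyses and power gives the analysis in two places:

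- The hypotheses are tested with a "hierarchical linear model analysis to test for significant differences between the two comparative groups (intervention and placebo) over time". Then: "Where there are significant group xtime interactions, planned contrasts will compare changes from baseline under each intervention".
- In the next paragraph, which mainly concerns associations between function, microbiota and metabolites: "All mixed models will include the subject as a random factor and time as a continuous covariate".

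The article does not limit the primary model to weeks 0 to 16, code visit as categorical, add a non-linear or off-treatment term, or name a week-16 between-group contrast as the primary test.

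**The concern.** A hierarchical linear model with repeated visits within participants is a mixed model, and the coding rule is stated for all mixed models without exception. With time as one continuous covariate, the group-by-time term is the difference between two straight-line slopes. If all four visits enter, that line is fitted through three on-treatment points and one point four weeks after dosing ended. It matches the week-16 effect for every pattern considered here only if the group difference keeps growing at the same rate after week 16. If the difference levels off or fades, week 20 pulls the slope down.

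The rule also sits badly with the planned contrasts. Under a purely linear time term, the modelled change at any visit is just slope times weeks, so there is no separate visit-specific change to contrast. Nor do the contrasts supply the missing primary test. They follow only a significant interaction, and they are described within each arm, not between arms.

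At stake is the test of every primary outcome, and of the secondary measures taken at all four visits, which are to receive similar tests. Measures taken only at baseline and week 16 (DXA, calf circumference) are unaffected, because a slope through two visits is the change between them.

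**Working it through.** **Inputs from the article.** Visits at weeks 0, 8, 16 and 20. Pre-post correlation 0.7. 37 per arm with about 30% dropout, so 37 × 0.7 = 25.9, taken as 26 completers per arm. Two-sided 5% (the sidedness is an assumption). Planned effect d = 1.2 for gait speed.

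**Assumptions, not in the article.** Week 20 enters the primary model. Complete data, random-intercept model, SD 1, the same correlation of 0.7 between every pair of visits. The share of the effect kept at week 20 is unknown, so a range is shown. An effect of D = 0.61 SD is chosen so that the week-16 contrast has about 80% power.

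The article gives no figure for this point to reproduce. Its total of 74 does not follow from d = 1.2: a plain two-sample t-test needs 12 per arm, 12/0.7 rounds up to 18, total 36. That is a separate matter, but it is why power is shown at both 0.61 and 1.2.

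**Step 1: what the slope estimates.** Mean time = (0 + 8 + 16 + 20)/4 = 11. Deviations are −11, −3, 5 and 9; their sum of squares is 121 + 9 + 25 + 81 = 236. For group differences d(t), slope = Σ(t − 11)d(t)/236. The ratio 16 × slope/D compares it with the week-16 effect D.

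| Difference at weeks 0, 8, 16, 20 (units of D) | Σ(t − 11)d(t) | 16 × slope/D |
|---|---|---|
| 0, 0.5, 1, 1 (linear, kept) | 12.5 | 0.85 |
| 0, 0.5, 1, 0.5 (linear, half lost) | 8 | 0.54 |
| 0, 0.5, 1, 0 (linear, all lost) | 3.5 | 0.24 |
| 0, 1, 1, 1 (complete by week 8, kept) | 11 | 0.75 |
| 0, 1, 1, 0.5 (complete by week 8, half lost) | 6.5 | 0.44 |
| 0, 1, 1, 0 (complete by week 8, all lost) | 2 | 0.14 |
| 0, 0.5, 1, 1.25 (same line continued) | 14.75 | 1.00 |

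Baseline is further from the mean time than week 20 (11 weeks against 9). The expected difference at baseline is zero, however, so week 20 carries the largest weight among the visits where an effect can appear.

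**Step 2: power.** SE of the week-16 contrast = √(4 × 0.3/26) = 0.215. SE of 16 × slope = 16 × √(2 × 0.3/(26 × 236)) = 0.158. Power ≈ Φ(effect/SE − 1.96).

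- Week-16 contrast, D = 0.61: 0.61/0.215 − 1.96 = 0.88, power 81%.
- Slope, linear and kept: 0.847 × 0.61/0.158 − 1.96 = 1.31, power 90%.
- Slope, linear, half lost: 0.542 × 0.61/0.158 − 1.96 = 0.13, power 55%.
- Slope, linear, all lost: 0.237 × 0.61/0.158 − 1.96 = −1.05, power 15%.
- Slope, same line continued after week 16: power 97%.
- At d = 1.2, linear build-up: about 98% (half lost) and 44% (all lost); the week-16 contrast is above 99%.

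**Step 3: the condition.** With weeks 0, 8 and 16 only, the mean is 8 and the sum of squares 64 + 0 + 64 = 128. The slope is 8D/128 = D/16 whatever the week-8 value, so 16 × slope = D. Its SE is 16 × √(0.6/(26 × 128)) = 0.215, the same as the contrast. With complete data the discrepancy vanishes.

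**The case against.** Four objections have weight.

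- **Week 20 is not expressly in the primary model.** The primary outcome and the hypotheses are framed on 16 weeks, and Step 3 shows that a model confined to weeks 0, 8 and 16 has no such defect. This stands as a condition on the whole point. Inclusion is nonetheless the natural reading, because the outcomes are measured at four visits, the test is over time and no restriction is given.
- **The coding rule may not be meant for the primary analysis.** It sits among correlations, structural equation models and stepwise regression, and the planned contrasts suggest visit-specific time. This also stands in part. Still, the rule says all, and the two paragraphs cannot both govern the same model.
- **The power loss depends on chosen values.** D = 0.61 is not the protocol's effect. At d = 1.2 the slope test is badly hurt only if the effect is wholly lost.
- **The direction is not uniform.** If the effect persists or grows after week 16, the slope test is the more powerful of the two under a linear build-up.

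A reader might infer that the plan certainly tests the wrong quantity, or that a product working only while taken will be declared ineffective. The article supports neither. It does not state that week 20 enters the primary test, gives no expected washout, and gives no purpose for the follow-up visit.

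**Conclusion.** The point holds conditionally. As written, the coding rule reaches the primary model, conflicts with the planned contrasts, and, if week 20 is modelled, replaces the week-16 between-group change with a slope across the off-treatment period. Under a linear build-up, 16 times that slope recovers 85%, 54% or 24% of the week-16 effect as it is kept, half lost or fully lost by week 20; for an effect complete by week 8 the figures are 75%, 44% and 14%.

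These ratios rest on complete data and a random-intercept model. The power figures also rest on 26 completers per arm, equal correlation of 0.7 and the effect size used. The mismatch in what is estimated does not need the effect to wane; the loss of power does.

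**What to change.** For the primary analysis, do one of the following:

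- Code visit as categorical (baseline, 8, 16, 20) with group-by-visit terms. Name the between-group difference in change from baseline at week 16 as the primary test, not conditional on a significant overall interaction. Report week 20 as a separate post-treatment contrast.
- Or restrict the primary model to weeks 0 to 16 and analyse week 20 separately.

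In either case, limit the continuous-time rule to the association models and bring the planned contrasts into line. Settle this before unblinding.

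The cost is wording and, for the first option, a few more model parameters; no visits, data or participants are added. There is some loss of power if the effect fully persists at week 20 (90% to 81% in the linear case above at 0.61 SD).

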### Secondary outcome measure: body composition

Dual-energy X-ray absorptiometry (DXA) will be used to measure whole and regional body composition, including lean body mass (LBM, g), appendicular lean mass (ALM, g), total and regional body fat mass (FM, %), and fat-free mass (FFM, g). Fasting whole-body scans (GE Healthcare Lunar iDXA, Madison, WI) will be acquired with participants in a supine position on the scanner table, wearing light clothing, with their limbs close to their bodies according to the manufacturer’s protocol. Segmental analyses of the whole body into arm, leg, and trunk segments will be separated with anatomical landmarks by the DXA analysis software. Appendicular skeletal muscle mass (ASMM) will be calculated as the sum of the lean soft tissue mass (LSTM) of both the right and left extremities, with the assumption that all non-bone and non-fat tissue is skeletal muscle [58]. Skeletal mass index (SMI) will be determined as the ALM divided by height squared (kg/m^2^) [59]. Body composition via DXA will be evaluated at baseline and week 16.

Body mass index (BMI), total body and segmental fat percent and weight, total body water percent and weight, total body and segmental muscle mass, and FFM will be estimated using bioelectric impedance analysis (BIA) with a multi-frequency body composition analyzer (Tanita MC-780U, Tokyo, JP) at 4 time points. Impedance will be analyzed in a fasting state, with participants standing barefoot on the electrode platforms, holding grips with both arms straight down at their sides.

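### The rule for mixed models names only a subject random factor and continuous time; read plainly, it implies equal correlation between visits and can make the group-by-time test too liberal

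*Protocol article*

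**What the plan says.** All references are to the protocol article.

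- *Statistical analyses and power*, paragraph on associations: "All mixed models will include the subject as a random factor and time as a continuous covariate". No other random term and no residual covariance structure is named.
- Same section, main analysis paragraph: the study hypotheses are addressed by a "hierarchical linear model analysis to test for significant differences between the two comparative groups". The interaction test then decides what follows: "Where there are significant group xtime interactions, planned contrasts will compare changes from baseline under each intervention".
- Same section, sample size paragraph: the only correlation given is an "assumed correlation of 0.7 between the pre- and post-intervention outcome measures".
- *Study duration*: after baseline, the visits are "mid-intervention at 8 weeks, an end-of-intervention visit at 16 weeks, and a follow-up visit at 20 weeks". The gaps are 8, 8 and 4 weeks, and the last visit falls after the intervention has ended. *Study assessments* puts the SPPB, handgrip strength and timed up-and-go at all four visits.
- Abstract, Methods: "The primary outcomes will be between-group changes in physical performance from baseline to 16 weeks".
- *Secondary outcome measure: body composition*: "Body composition via DXA will be evaluated at baseline and week 16". Calf circumference is likewise measured only at these two visits.

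**The concern.** A model whose only random term is the subject, with independent residuals, allows one correlation for all pairs of visits. It treats weeks 16 and 20 as no more alike than weeks 0 and 20. It also leaves no room for people to differ in their underlying rate of change. If either restriction is false, the within-person residual variance is the wrong yardstick for a difference in slopes, and the standard error of the group-by-time term comes out too small.

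That term is the gate to the planned contrasts for the main hypotheses, so an understated standard error raises the chance of a false positive at the point where the plan first looks for an effect. The Benjamini–Hochberg step does not repair this, because it takes each p-value as valid.

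This is separate from whether a straight line through week 20 describes the mean well. The standard error can be wrong even when the mean trend is right.

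**Working it through.** **Inputs from the article.** Visits at weeks 0, 8, 16 and 20; 37 per arm; about 30% dropout, so 37 × 0.7 = 25.9, taken as n = 26 per arm; pre-post correlation 0.7; nominal level 5%, taken as two-sided. Nothing here depends on how the total of 74 was derived.

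**Inputs that are assumptions.** The pattern of correlation across the four visits, any variation in slopes between people, and the share of measurement error. The article gives none of these, so a range is shown.

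**Formulas.** Mean visit time is 44/4 = 11 weeks, so the centred times are c = (−11, −3, 5, 9) and c′c = 121 + 9 + 25 + 81 = 236. Let V be the true covariance over the four visits, with baseline variance 1.

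- True within-person variance in the slope direction: A = c′Vc / 236.
- Average within-person variance, which the random-intercept model uses instead: B = (trace V − sum of all entries of V / 4) / 3.
- Expected residual variance after fitting a slope in each arm: s² = (2n·3B − 2A) / (6n − 2).
- Model SE / true SE = √(s²/A).

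**Step 1: the plan's own 5%.** With equal correlation 0.7, A = B = 0.3, the SE ratio is 1.00 and the simulated type I error is 5.1%. The model is sound if its assumption holds.

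**Step 2: pure exponential decay, 0.7 at 16 weeks.** Correlations are 0.7^(gap/16): 0.915 (4 weeks), 0.837 (8), 0.765 (12), 0.700 (16), 0.640 (20).

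- c′Vc = 236 + 2(33×0.837 − 55×0.700 − 99×0.640 − 15×0.837 − 27×0.765 + 45×0.915) ≈ 103.3, so A = 103.3/236 = 0.438.
- The sum of all entries is 4 + 2×4.694 = 13.387, so B = (4 − 3.347)/3 = 0.218. A/B = 2.01.
- s² = (52×0.653 − 2×0.438)/154 = 0.215. SE ratio = √(0.215/0.438) = 0.70.
- The critical value 1.975 (154 df) acts like 1.975×0.70 = 1.38, so the type I error is about 2(1 − Φ(1.38)) ≈ 17%. Simulation gives 16.5–17%, and a REML fit rejected in 54 of 300 runs (18%).

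**Step 3: milder cases.** If slopes vary with SD s per 16 weeks (in outcome SDs) on top of equal correlation, A = 0.3 + 236s²/256 and B = 0.3 + 236s²/(3×256). For s = 0.5, 236×0.25/256 = 0.230, so A = 0.530 and B = 0.377.

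| Assumed truth (26 per arm) | Corr. weeks 0–16 | A/B | SE ratio | Type I error |
|---|---|---|---|---|
| Equal correlation | 0.70 | 1.00 | 1.00 | 5.1% |
| Slope SD 0.2 | 0.69 | 1.08 | 0.96 | about 6% |
| Decay, 25% measurement error | 0.70 | 1.14 | 0.94 | 6.4% |
| Slope SD 0.3 | 0.67 | 1.17 | 0.92 | 7.0% |
| Partial decay (0.5 constant, 0.3 decaying to 0.3 of itself at 16 weeks, 0.2 noise) | 0.59 | 1.34 | 0.86 | 9.0% |
| Slope SD 0.5 | 0.63 | 1.41 | 0.84 | 9.7% |
| Decay, 15% measurement error | 0.70 | 1.45 | 0.83 | 10.5% |
| Pure decay, no measurement error | 0.70 | 2.01 | 0.70 | 16.5–17% |

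Where recomputed with 37 per arm, the results are nearly the same (for example, 17.0% under pure decay).

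**Step 4: what repairs it.** A test that lets each person have their own slope (a two-sample t test on per-person slopes, complete data) holds close to 5% in every scenario (5.0–5.4%). Making time categorical but keeping only a random intercept does not repair it. Under pure decay, the week-16-minus-baseline contrast still rejects 9.2–9.7% of the time, and week 20 minus week 16 rejects only about 0.2%.

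**The case against.** The strongest reply is about the text. The article says mixed models will *include* a subject factor; it does not say that this is the only random term or that residuals are independent. A hierarchical linear model may carry random slopes, and covariance structure is often left to the full protocol or SAP, neither of which is shown. A reader might infer that the plan forces equal correlation or rules out random slopes. The article does not support that, and the point is not made in that form. What remains is that the article does write a rule for all mixed models, names one random term, and gives time no other role than that of a covariate. That is a stated model with a natural plain reading, not silence. The sentence stands in the paragraph on associations, but its wording reaches the main analysis.

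A reader might also infer that the main test has a 17% false-positive rate. That figure needs pure decay with no measurement error. Gait speed, handgrip and timed up-and-go are all taken as the best of repeated attempts, which suggests some trial-to-trial noise. As measurement error rises to 30%, the decay scenario becomes exact equal correlation and the inflation vanishes. Nor does the article show that equal correlation is implausible: participants are healthy or have stable disease, and follow-up is 20 weeks. The size is therefore conditional.

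The scope objection stands in full. With only two visits there is a single correlation, so DXA and calf circumference are unaffected.

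Finally, the proposed remedy goes further than this defect alone requires, since a random slope would be enough for the slope test. That is correct. Categorical visit is preferred for the primary outcomes because the stated comparison is baseline to week 16.

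**Conclusion.** The point holds in a conditional form. As written, the rule reads as a random intercept with linear time. For the four-visit outcomes, the group-by-time test under that model is valid only if all pairs of visits are equally correlated. Any decay in correlation or variation in slopes of the kinds examined makes the test too liberal. With 26 per arm, the type I error runs from about 5% (equal correlation), through 6–7% (mild departure) and roughly 9–10% (moderate), to 17% (pure decay without measurement error). These rest on assumed covariance patterns, complete data and a two-sided test; the article's single correlation of 0.7 cannot say which pattern applies. The direction is firm and the size is not. It is worth correcting because the test concerned is the gate for the main hypotheses and the correction is cheap.

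**What to change.** For the primary outcomes, replace the sentence with: visit as a categorical factor, a group-by-visit interaction, and an unstructured covariance over the four visits, with the between-group week-16 contrast estimated from that model. In SPSS MIXED this is a REPEATED statement with type UN and Satterthwaite degrees of freedom. Both parts are needed, since categorical visit with only a random intercept leaves the week-16 contrast exposed. Wherever a linear time slope is kept, as in the association analyses, add a subject-level random slope. Two-visit outcomes need no change on this account.

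The cost is one sentence of specification and ten covariance parameters (4×5/2) in place of two, which 52 (2×26) to 74 participants with four visits can support. If the full protocol or SAP already specifies such a model, the article's sentence need only be corrected to match it.
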